### Statistical Considerations

| ***Sample Size Justification:*** Our analysis will be based on a longitudinal regression analysis in which we do not have an estimate of the within-participant correlations. In the worst case, the two follow-up measures provide no more information than a single follow-up, and the power calculation is equivalent to that for a simple t-test. With 30 participants in each group, we would have 50% power to detect an effect size of 0.52 (i.e., the sample size provides 50% sensitivity to detect a difference between groups .52 times the standard deviation of the outcome measure) and 80% power to detect an effect size of 0.74 for each of the main effects. Our primary hypothesis, however, is an interaction effect. Our sample size provides at least 50% power to detect an interaction effect size of 1.03, under this worst-case scenario. At the other extreme, if the two follow-up observations are independent, we will have 50% power to detect an interaction effect size of 0.72 and 80% power to detect an effect size of 1.03. The use of regression models further increases power by accounting for additional sources of variability. In our heart failure study, the mean difference in MSE change between Tai Chi and control was 2.26, which translates to an effect size of 1.2. Preliminary COP data from our Tai Chi for osteopenia study showed a similar effect. Therefore, we think changes of this magnitude will likely be present in the proposed study and our study has adequate power.  For Study Aim 3, we will in essence be comparing the 30 tai chi experts to the 60 novices. After adjusting for the effect of age, we will have 80% power to detect a difference between naïve and tai chi experts of approximately 0.65 times the residual error.  For Study Aim 4, we will be comparing the baseline COP and balance measures in the various age categories (15 participants age 25-35, and 20 participants in each of the older groups). This sample will provide at least 82% power to detect a difference between the young group and the average of the older groups equal to the within-group standard deviation.  ***b. Data Analysis***  *Aim 1*: We are interested in comparing the change over time in the Tai Chi students versus the controls. The primary analysis will use an intention-to-treat paradigm, i.e., participants will be evaluated on the basis of group assigned by randomization without regard to subsequent adherence. Since this is a pilot study, we will not impute values for missing data; however, the statistical models we are using will include all available data. We recognize that some participants may drop out before the follow-up evaluation and that some outcome measures may not be evaluable for some participants. We will make no adjustment for multiple testing. A secondary ‘per-protocol’ analysis will be limited to participants who were compliant (attended 70% of classes and completed at least 70% of home sessions).  Our primary analysis will employ linear mixed effects regression models that examine change over time (i.e., slope) for each outcome measure (i.e., the complexity measures, MSE and detrended fluctuation analysis) for each of the systems (i.e., heart rate, balance and gait). The models will incorporate a random intercept and a random slope for each participant. The models will be of the form:  ****  for individual  in treatment group  where the random intercept , the random slope , and the residual error . The focus of the primary analyses is on , which evaluates whether treatment is associated with the slope over time.  We will also conduct sensitivity analyses that incorporate additional covariates into the models, including age, gender, baseline physical and mental health, BMI, expectancy, and exercise behavior. We are particularly interested in examining age with a focus on assessing whether age substantially reduces the variability of the random effects, i.e., whether it explains a substantial proportion of between-person variability in baseline complexity and slope.  Analyses of secondary outcomes will follow the same general analytic approach. We will use mixed effects models to examine the effects of Tai Chi training over time on physical and cognitive function (exercise capacity, balance, upper and lower extremity strength, cognitive function, and quality of life) and adaptive capacity (change in heart rate, change in COP displacement, change in stride variability).  *Aim 2*: We hypothesize that function and adaptive capacity are associated with complexity. We will first examine the association between complexity measures and function/adaptive capacity at baseline. We will calculate Pearson correlation coefficients between the complexity measures (MSE and detrended fluctuation analysis) and the measures of function/adaptive capacity. To examine the independent association between complexity and function/adaptive capacity, we will fit ordinary least squares regression models using the function/adaptive capacity measures as the dependent variable. Independent variables will include age and sex as well as any other baseline characteristics associated with the function variable. We will add the complexity measure to this model and evaluate the Wald test and the change in R^2^.  We will also investigate whether changes in complexity are associated with changes in function/adaptive capacity. We will fit linear regression models with change in function/adaptive capacity as the dependent variable and change in complexity as the independent variable of interest. Since we will have 2 observations per participant (change at 3 months and change at 6 months), we will use generalized estimating equations methods (GEE) to account for the within-person correlation. Independent variables will include the measure of function/adaptive capacity at baseline, age, sex, treatment group and time (3 vs. 6 month).  Further, we hypothesize that complexity is the primary mediator of the association between Tai Chi and improvements in adaptive capacity. We will examine this using the approach recommended by Judd and Kenny.^193^ For example, to examine whether multi-scale entropy of balance mediates the effect of Tai Chi on center of pressure response to a dual cognitive task among the older participants, we will fit 3 regression models: regress MSE on Tai Chi use; regress COP response on Tai Chi; and regress COP response on MSE and Tai Chi use. The associations seen in these models determine the existence and strength of mediation.  Despite the implicit directionality of our hypotheses, all tests will be two-sided. We recognize that we are examining a moderate number of outcomes in this study. Since it is a pilot study and has limited power, we do not intend to adjust for multiple testing.  *Aim 3:* Our goal is to compare the complexity measures, function, and resilience to perturbations between tai chi experts and those with no tai chi training or only limited training. We expect responsiveness to decrease as a function of age among the tai chi naïve participants (i.e., both randomized groups combined). We hypothesize that tai chi experts will have a generally higher level of responsiveness, and that their responsiveness will decline with age at a slower rate than naïve or novice practitioners. To examine these questions, we will fit linear regression models to the baseline responsiveness measures for all participants:    where TC is an indicator variable for the tai chi experts.  is an estimate of the difference in responsiveness between tai chi experts at age 50,  is an estimate of the change in responsiveness per year for the novice group, and is the difference in rate of change between novices and tai chi experts.  We will fit a similar model to compare the tai chi experts to the naïve and novice groups using the 6-month data for the randomized patients and the baseline data for the tai chi experts. The group variable will be a categorical variable with 3 levels.  *Aim 4:* We will calculate sample means for each of the outcomes in each age group. We will use standard one-way analysis of variance to compare the four groups. If the overall test is significant, we will use Dunnett’s test to compare the young group to each of the older age groups. |

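### Aim 2 reads mediation from three regressions, one of them a total-effect model, with no interval for the indirect effect and no support for calling complexity the primary mediator

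*Protocol*

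**What the plan says.** The passage is in the Protocol, B3, Statistical Considerations, Data Analysis, Aim 2.

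- **Hypothesis:** "we hypothesize that complexity is the primary mediator of the association between Tai Chi and improvements in adaptive capacity".
- **Method:** an approach taken from a cited methods paper (reference 193). The worked example is MSE of balance as mediator of the COP response to a dual task, with three models: "regress MSE on Tai Chi use; regress COP response on Tai Chi; and regress COP response on MSE and Tai Chi use".
- **Conclusion drawn from:** "The associations seen in these models determine the existence and strength of mediation".

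The passage names no estimate, interval or test of the indirect effect, no proportion mediated and no criterion for *primary*. It also sets no significance threshold for any of the three models. No power is given for this analysis. The sample size paragraph gives power for group differences only: "With 30 participants in each group, we would have 50% power to detect an effect size of 0.52" and "80% power to detect an effect size of 0.74 for each of the main effects". For the Tai Chi effect on MSE it cites a heart failure study: "the mean difference in MSE change between Tai Chi and control was 2.26, which translates to an effect size of 1.2". The same section calls the trial a pilot with limited power and makes no multiplicity adjustment.

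**The concern.** Mediation means that the indirect effect is not zero. That effect is the Tai Chi effect on MSE (path a) times the MSE effect on COP response given Tai Chi (path b). The second of the three models addresses a different null, namely no total effect of Tai Chi on COP response. If complexity carries the whole effect, the total effect is a×b, and 30 per arm gives little power to detect it. An analyst who takes all three associations as the test of existence could report no mediation when complexity is in fact the full mediator.

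The other risk concerns *primary*. With these models the natural shortcut is to see whether the Tai Chi coefficient loses significance once MSE is added. At this sample size that happens often even when most of the effect bypasses complexity. The pilot is meant to inform a later trial, including its choice of biomarkers, so either misreading would carry forward.

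**Working it through.** **1. Protocol power figures.** With 30 per arm, the standard error of a difference in SD units is √(1/30 + 1/30) = 0.258. Alpha is not stated; two-sided 0.05 is assumed. From the noncentral t with 58 df:

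- d = 0.52: ratio 0.52/0.258 = 2.01, power 50.8% (stated 50%).
- d = 0.74: ratio 0.74/0.258 = 2.87, power 80.5% (stated 80%).
- Interaction, worst case: 1.03/2 = 0.515, power 50.1% (stated 50%).
- Interaction, independent follow-ups: 0.72/√2 = 0.509, power 49.2% (stated 50%); 1.03/√2 = 0.728, power 79.2% (stated 80%).

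All of them reproduce, so sample size and alpha are read correctly.

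**2. Model for the mediation check.** M = aX + N(0, 1) and Y = bM + c′X + N(0, 1 − b²), where X is Tai Chi or control, M is MSE and Y is COP response. From the protocol: 30 per arm, a = 1.2 and a = 0.74. Assumed: b = 0.3 to 0.5, one follow-up value per person, no dropout, and c′ = 0 (full mediation) to begin with.

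**3. Why the total effect is the weak link.** Under full mediation the total effect is a×b, and Y has within-arm variance b² + 1 − b² = 1. At a = 1.2, b = 0.3 the expected ratios of effect to standard error are:

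- Path a: 1.2/0.258 = 4.65.
- Path b: standard error about √(0.91/58) = 0.125, so 0.3/0.125 = 2.4.
- Total effect: 0.36/0.258 = 1.39.

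By the normal approximation the last gives P(Z > 1.96 − 1.39), about 28% power.

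**4. Simulated power, full mediation.** The three-test and a-and-b columns use 20,000 runs. The bootstrap column uses 1,500 runs, with a simulation standard error of at most √(0.25/1500) = 1.3 points.

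| a | b | a×b | all three significant | a and b only | bootstrap CI of a×b |
|---|---|---|---|---|---|
| 1.2 | 0.3 | 0.36 | 17% | 65% | 66% |
| 1.2 | 0.4 | 0.48 | 39% | 89% | 89% |
| 1.2 | 0.5 | 0.60 | 62% | 98% | 98% |
| 0.74 | 0.3 | 0.22 | 8% | 52% | 54% |
| 0.74 | 0.4 | 0.30 | 16% | 72% | 71% |
| 0.74 | 0.5 | 0.37 | 27% | 79% | 81% |

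A separate run gave 18–61% against 66–98% at a = 1.2, and 8–26% against 55–82% at a = 0.74. The total-effect test alone had 13–63% power across these settings.

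**5. How far the assumptions matter.**

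- With a direct effect of 0.3 SD in the same direction and a = 1.2, the three-test rule reaches 44%, 74% and 92% for b = 0.3, 0.4 and 0.5.
- With unit residual SDs and a = 1.2, stronger paths b = 0.59 and 0.80 give 63% and 81%, against 98% and 99.6% for an interval on a×b.
- On that same scaling, a = 1.2 and b = 0.39 give 31% against 83% at 30 per arm, and 23% against 76% at 25 per arm.
- Also on that scaling, at a = 0.5 the interval itself has only 21–50% power. Part of the weakness there is sample size, not method.

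**6. False positives.** With a true indirect effect of zero, requiring a and b both significant rejected in 4.4–5.1% of trials. The percentile bootstrap rejected in about 5–8% where one path was non-zero.

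**7. The word *primary*.** Take a = 0.8, b = 0.3, c′ = 0.56. The indirect effect is 0.24 and the total 0.80, so 0.24/0.80 = 30% is mediated. The direct effect is still non-significant in about 46% of trials. A stricter rule fares badly too. Requiring the lower limit of the proportion mediated to exceed 0.5 succeeds in only 0.5%, 4% and 15% of full-mediation trials at a = 1.2, and in 0.1–1.5% at a = 0.74.

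**The case against.** The strongest reply is that the power loss belongs to a rule the protocol does not contain. The passage lists models and says their associations decide the matter. It does not say that all three must be significant, nor that the direct effect must fade. A reader might infer that the plan makes a significant total effect a condition; the text does not say so. Paths a and b from the first and third models nearly match the bootstrap (table), with error near 5%. So the stronger claims that existence has no valid test, or that a true mediator would usually be missed, are not supported. The second depends on a path b that the protocol does not give, and it fails when b is strong.

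The total-effect model also has a proper place. The hypothesis is about an association that the trial sets out to test (H.1.c). In linear models on the same participants, total minus direct effect equals a×b exactly, so the fitted models contain the indirect effect. Nor is the total effect always smaller than either path: at a = 1.2, b = 0.3 it is 0.36, above b. It is the hardest to detect because of its standard error.

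Finally, an interval method and a threshold can be left to a statistical analysis plan, which is not at hand. All of this stands. What it does not answer is that the protocol itself fixes how mediation is to be concluded, counts the total-effect model among the deciding associations, and does not say how to conclude when that model disagrees with the other two.

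**Conclusion.** The point holds in a limited form. Mediation is to be judged from three sets of associations, one of which addresses the total effect. No indirect effect with an interval is planned, and nothing supports a claim that complexity is the primary mediator. If the three associations are applied jointly, power to find a true full mediator falls by roughly 36 to 56 points: at a = 1.2 from 98 to 62 (36 points) up to 89 to 39 (50 points), and at a = 0.74 from 54 to 8 (46 points) up to 71 to 16 (55 points) and 81 to 27 (54 points). This rests on b between 0.3 and 0.5, no direct effect, one follow-up value per person and alpha 0.05. The loss is smaller with a stronger b or a same-direction direct effect, and it disappears if only the first and third models decide existence. *Primary* is not determinable at 60 participants by either rule examined. No primary outcome is affected; this is a secondary question in a pilot, and the change is advisable rather than essential.

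**What to change.** Replace the concluding sentence of the mediation paragraph with wording to this effect:

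- The mediation conclusion rests on the indirect effect, the product of the Tai Chi coefficient in the MSE model and the MSE coefficient in the model containing both, with a 95% bootstrap CI resampled by participant within arm.
- A significant total effect of Tai Chi on COP response is not required. That model is still reported.
- The direct effect and the proportion mediated are reported with CIs as descriptive estimates.
- The primary-mediator conclusion is dropped, or reported as not determined at this sample size. It is not inferred from the direct effect losing significance.

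The cost is one paragraph and a bootstrap on data already collected, with no extra participants or measurements. The drawbacks are that the percentile bootstrap is slightly liberal at 60 participants (about 5–8% in the null settings above) and that the proportion mediated will be imprecise.

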# B1. PURPOSE OF PROTOCOL

| To evaluate the effects of Tai Chi—a mind-body exercise––on age-related loss of physiological complexity (using fractal and entropy based measures), and to understand the relationship between complexity, function and adaptability, we will conduct a two-arm prospective randomized clinical trial. Our overarching goal is to evaluate if six months of Tai Chi training, compared to a waitlist control receiving standard medical care, can enhance physiological complexity and adaptability in older Tai Chi-naïve adults. Secondary goals of the study are to characterize the relationship between complexity biomarkers, measures of function, and resilience. This pilot study will inform a future more definitive trial by providing information on recruitment and retention, compliance, dose-dependent effects, preliminary estimates of effect size, and the optimal biomarkers of complexity, function, and adaptive capacity.    **Specific Aim #1: To determine if 6 months of Tai Chi training can increase complexity, function, and adaptive capacity of multiple physiological systems in older healthy adults.** Sixty healthy older adults (50-79y) naïve to Tai Chi will be recruited from the Boston community and randomized to either 6 months of Tai Chi training or to a waitlist control. Measurements of complexity, adaptive capacity, and function will be assessed at baseline, 3, and 6 months. Dynamics of cardiovascular (heart rate), balance (center-of-pressure displacement), and locomotor (gait stride interval) systems will be quantified using indices derived from two complementary analytic methods developed by members of our team––detrended fluctuation analysis^26^ and multi-scale entropy.^6^ Function will be characterized by exercise capacity, clinical measures of balance, lower and upper extremity strength, cognitive function, and health related quality of life. Adaptability of multiple physiological systems will be assessed using common perturbations including: heart rate responses to posture change, center of pressure (i.e. balance) responses to a dual cognitive task and closed eyes, and c) gait responses to dual cognitive task. In addition to informing the feasibility of a future trial, outcomes will provide preliminary data to evaluate the following hypotheses.  ***Hypotheses*** *Compared to the control group:*  *H.1.a) Those who participate in Tai Chi will exhibit higher levels of complexity across all measured physiological systems;*  *H.1.b) Those who participate in Tai Chi will exhibit higher levels of physical and cognitive function;*  *H.1.c) Those who participate in Tai Chi will exhibit higher levels of adaptive capacity;*  *H.1.d) The magnitude of the effects of Tai Chi on physiological complexity, function and adaptive capacity in healthy older adults will be positively correlated with age.*  **Specific Aim #2: To determine the relationships between biomarkers of physiological complexity, conventional measures of function and adaptive capacity.** Statistical regression models will be used to determine relationships, both at baseline and overtime, between a) complexity biomarkers and measures of physical and cognitive function, and b) complexity biomarkers and adaptive capacity. Elucidating these relationships will further inform the interpretation of complexity biomarkers and provide insights into underlying component mechanisms contributing to complex physiological dynamics.  ***Hypotheses*** *At baseline:*  *H.2.a) Measures of complexity are positively correlated with physical and cognitive function;*  *H.2.b) Measures of complexity are positively correlated with adaptive capacity.*  *Over time:*  *H.2.c) Changes in complexity are positively correlated with changes in physical and cognitive function;*  *H.2.d) Changes in complexity are positively correlated with changes in adaptive capacity.*  **Specific Aim #3: To determine cross-sectionally if long-term Tai Chi training (> 5 years) is associated with greater complexity, function, and adaptive capacity of multiple physiological systems in older healthy adults, when compared with Tai Chi naïve and novice (≤ 6 months training) Tai Chi practitioners**  ***Hypotheses*** *Compared to Tai Chi naïve and novice Tai Chi practitioners:*  *H.3.a) Long-term Tai Chi practitioners will exhibit higher levels of complexity across all measured physiological systems;*  *H.3.b) Long-term Tai Chi practitioners will exhibit higher levels of physical and cognitive function;*  *H.3.c) Long-term Tai Chi practitioners will exhibit higher levels of adaptive capacity;*  *H.3.d) The magnitude of the effects of long-term Tai Chi training on physiological complexity, function and adaptive capacity in healthy older adults will be positively correlated with age.*  **Specific Aim #4: To determine cross-sectionally if age is associated with greater complexity, function, and adaptive capacity of balance and gait in young healthy adults, when compared with to older adults**  ***Hypotheses*** *Compared to older adults and a young adult comparison group:*  *H.3.a); The magnitude of physiological complexity, function and adaptive capacity will be positively correlated with age.*  *H.3.b) Young adults will exhibit higher levels of adaptive capacity of balance and gait.* |

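### Aim 3: the stated 0.65 belongs to an age-averaged expert difference, but the only level coefficient the protocol defines is the difference at age 50, which is about half as precise

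*Protocol*

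**What the plan says.** All of the following is in the Protocol.

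- **Statistical Considerations, Sample Size Justification.** "For Study Aim 3, we will in essence be comparing the 30 tai chi experts to the 60 novices". The power claim, made for a comparison that allows for age, reads: "we will have 80% power to detect a difference between naïve and tai chi experts of approximately 0.65 times the residual error".
- **Statistical Considerations, Data Analysis, Aim 3.** A linear regression is fitted to the baseline measures with an indicator for experts. Three coefficients are described. The first is "an estimate of the difference in responsiveness between tai chi experts at age 50". The second is the yearly change in the novice group. The third "is the difference in rate of change between novices and tai chi experts". A similar model with a three-level group variable is planned for the 6-month data.
- **B1, Purpose of Protocol.** H.3.a-c claim higher levels in long-term practitioners, with no restriction to any age. H.3.d adds an age trend: "The magnitude of the effects of long-term Tai Chi training on physiological complexity, function and adaptive capacity" is expected to rise with age. The Aim 3 analysis text agrees, expecting experts to decline more slowly than the others.

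Both groups are recruited at ages 50 to 79 (Subject Selection). The Data Analysis section states that "all tests will be two-sided". It gives no alpha.

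**The concern.** The sample size text and the analysis text describe two different quantities. The first is one group difference adjusted for age. The second is a model in which the group difference changes with age, so the expert coefficient is the difference at the single age from which age is measured, here 50.

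That age is the edge of the data, where a fitted difference is least precise. It is also where the protocol's own hypothesis puts the smallest gap. H.3.a-c are claims about level across the whole age range. An analyst who reads them off the one level coefficient described would be using an imprecise quantity with an expected value below the average gap, and could report no expert advantage when an average advantage of the planned size exists.

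**Working it through.** **Inputs.** From the Protocol: 30 experts, 60 naïve participants, ages 50-79 in both groups, two-sided tests, 80% power. The Aim 4 power statement counts 20 participants in each older age group, which supports a roughly even spread for the 60.

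Assumed: alpha 0.05; the experts' age distribution, which is not given (varied below); and the model form, namely expert indicator, age minus 50, and their product. The equation is not in the extracted text, so this form is inferred from the coefficient descriptions and should be checked against the printed equation. All figures are in residual SDs.

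**1. Reproduce the 0.65.**

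SE of the age-averaged difference = sqrt(1/30 + 1/60) = 0.2236.

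Detectable difference, normal approximation: 0.2236 × 2.802 = 0.626, where 2.802 is the sum of the normal quantiles 1.960 and 0.842. With the noncentral t on 87 df it is 0.633, and power at 0.65 is 82%.

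Exactly 0.65 needs a variance inflation of (0.65 ÷ 0.6335)² = 1.05, which a group-age correlation of about 0.22 would produce. A one-sided test would give 0.556 and does not fit. So the 0.65 is sound for an age-adjusted, age-averaged difference.

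**2. SE of the expert coefficient at age 50.** When both groups have the same mean age m,

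Var(a) = 1/30 + 1/60 + (m − a)² × (1/SSx_experts + 1/SSx_naïve),

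where SSx is the sum of squared age deviations within a group. With ages evenly spaced over 50-79, m = 64.5, SSx_experts = 2247.5 and SSx_naïve = 4347.5.

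- At a = 64.5: Var = 0.05, SE = 0.224.
- At a = 50: (m − a)² = 210.25. The two age terms are 210.25 ÷ 2247.5 = 0.0935 and 210.25 ÷ 4347.5 = 0.0484, which sum to 0.142. Adding the 0.05 gives Var = 0.192, SE = 0.438.

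The ratio is 0.438 ÷ 0.224 = 1.96.

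**3. Consequences (noncentral t, 86 df).**

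| Quantity | SE | Detectable at 80% | Power at a constant 0.65 |
|---|---|---|---|
| Difference at mean age | 0.224 | 0.63 | 82% |
| Difference at age 50 | 0.438 | 1.24 | 31% |

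Normal check on the last cell: 0.65 ÷ 0.438 = 1.48, and Φ(1.48 − 1.96) is about 0.32.

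If the gap at 50 were half the average (0.325, an illustrative reading of H.3.d), power on the age-50 coefficient would be about 11%.

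**4. Sensitivity to the assumed ages (same shape in both groups).**

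| Assumed ages | SE ratio | Detectable at 50 | Power at 0.65 |
|---|---|---|---|
| Even, interval midpoints | 2.00 | 1.27 | 30% |
| Younger-skewed, mean about 61 | 1.85 | 1.17 | 34% |
| Bell-shaped, mean 65 | 2.46 | 1.56 | 21% |
| Older-skewed, mean about 69 | 3.02 | 1.91 | 16% |

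Another younger-skewed shape gave a ratio of 1.8 and power of 36%. With opposite skews in the two groups the ratio was 2.0 to 2.3. No spread tried brought the age-50 coefficient near 80%.

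**5. Effect of centring.** With age centred at the pooled mean and the product term kept, the SE is 0.224 and the detectable difference 0.634 whenever the two groups share an age distribution. The fitted values, the residuals and the interaction test do not change.

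**The case against.** A reader might infer that the protocol tests H.3.a-c at age 50, so that Aim 3 would usually miss the difference it was sized for. The documents do not go that far. The coefficient is called an estimate, and Aim 3 names no test, whereas Aim 2 names a Wald test and Aim 4 an analysis of variance followed by Dunnett's test.

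The age-averaged difference can be computed from the same fit. A joint two-df test of group and group-by-age is equally compatible with the text. With evenly spread ages it has about 73% power for a constant 0.65, and about 76% if the gap is 0.325 at age 50 and reaches 0.65 at mean age. The 31% therefore holds only if the age-50 coefficient is the one used.

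A reader might also infer that the 0.65 is wrong. It is not: it reproduces for the age-averaged difference, and the sample size wording already points to that quantity.

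It can further be said that the choice of contrast belongs in a statistical analysis plan, and that Aim 3 is a non-randomised comparison within a pilot. The second point lowers the importance. The first does not remove the finding, because the protocol itself chooses age 50 as the reference and gives that coefficient its meaning. What remains is a mismatch between two statements in the same section, with no other level contrast named.

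**Conclusion.** The point holds as a mismatch of moderate importance. The stated power belongs to the age-averaged expert difference, while the only level coefficient described is the difference at age 50.

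If H.3.a-c are judged on that coefficient, its SE is about twice as large with evenly spread ages (about 1.8 to 3 times over other assumed spreads). Power at a constant 0.65 falls from 82% to about 31% (range 16% to 36%), and the detectable difference rises from 0.63 to about 1.24. If H.3.d is true, the gap at 50 is below the average gap and power is lower still.

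This rests on the inferred model form, two-sided alpha 0.05 and assumed expert ages. The SE ratio does not depend on alpha. The randomised Aim 1 comparison is not affected.

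**What to change.** In the Aim 3 analysis text:

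1. Centre age at the pooled mean (about 65), or keep age measured from 50 and name the age-averaged expert-naïve difference as the quantity for H.3.a-c.
2. Keep the product term, and state that it addresses H.3.d.
3. State in the sample size paragraph that the 0.65 refers to the averaged difference.
4. Complete the coefficient description, which says the difference is between experts but not with whom they are compared.
5. Make the same choice in the three-group 6-month model. With 30 per group, no losses and evenly spaced ages, the SE for experts against either other group is sqrt(2/30) = 0.258 at mean age, but sqrt(2/30 + 210.25 × 2/2247.5) = 0.504 at age 50.

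The cost is a few sentences. No data, visits or participants are added.
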